#### Hearing

Pure tone audiometry will be performed at baseline, after 6 months and after a year. In line with the guideline of AAO HNS 1995 guideline,^17^ we will use the average scores of four-tone audiometry at 0.5, 1, 2 and 3 kHz and we will assess the word recognition scores as the percent correct score at the presentation level in decibel. A decrease of ≥10 dB or a change in word recognition score of ≥15% points is considered clinically significant.

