### Sample size

A sample size calculation was performed based on recommendations as summarised in the Clinical Practice Guideline for Menière’s disease.^1^ An expected proportion of subjects achieving vertigo control of 87.5% was assumed for methylprednisolone treatment compared with an assumed 67.5% for placebo, that is, a difference in treatment effect of 20%. With a statistical power (1-β) of 80% and a type 1 error (α) of 5%, 67 patients per group are required. With an estimated 10% loss-to-follow-up, 74 patients will be included in each arm, giving a total sample size of 148. In total, over the six participating centres, 340 MD patients yearly visit the Otolaryngology department and will be screened for the trial. It is expected that 15% will meet the inclusion criteria and will be willing to participate. This will result in approximately 50 eligible patients for inclusion per year.

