### Randomisation and blinding

Subjects will be randomly assigned to either methylprednisolone or placebo with a 1:1 allocation as per computer-generated random sequence, stratified by site generated by Castor EDC. Blinding will be maintained until all subjects have finished their treatment phases. All study participants, participating medical professionals and outcome assessors will be blinded. The independent epidemiologist and pharmacy personnel will both be unblinded during randomisation and therapy allocation.

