#### Tinnitus

The Tinnitus Functional Index (TFI) measures the impact of tinnitus on daily life.^21^ This survey will be administered at baseline, after 6 months and after a year. One point decrease of increase will be defined as improved or worsened tinnitus respectively.^22^

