### Statistical analysis

Ordinal regression using mixed model analysis will be used to analyse the primary outcome (ie, class of vertigo). In addition, generalised estimating equation analysis of the actual vertigo attacks recorded using the DizzyQuest app will be used to estimate the incidence rate ratio for comparison between the methylprednisolone and placebo groups. A decrease of 100% is considered total control of vertigo episodes, while a reduction of >40% is considered a substantial and thus clinically relevant reduction.^17^

Mixed model analysis will be used to analyse differences in the questionnaire scores (DHI, TFI, FLS, eQ-5D/VAS, iMCQ, iPCQ) between the two groups. Logistic regression analysis will be used to analyse the remaining secondary outcomes (incidence of escape interventions, hearing loss and adverse events). A reduction in hearing of 10 decibels or a 15% change in word recognition will be regarded as a clinically significant difference.^17^

Subgroup analyses will be performed with regard to sex, duration of the disease and the type of MD (delayed MD, familial MD and autoimmune MD). These subgroups will be defined as described in Frejo *et al*.^25^ Two sensitivity analyses will be carried out in addition to the intention to treat analysis: a per protocol analysis in which patients who received additional co-interventions to achieve vertigo control are excluded; and an as-treated analysis in which participants who received additional co-interventions are analysed.

In order to evaluate the average costs and outcomes between the methylprednisolone and placebo groups for the cost-effectiveness analysis, intention-to-treat and net-benefit analysis will be used. For all statistical analysis, multiple imputation to adjust for missing data will all be used.^26^ QALYs will be calculated using the Dutch tariff for the EuroQoL EQ-5D-5L^23^ and as sensitivity analysis, the visual analogue scale valuing health, with power-transformation.^27^ All outcomes with corresponding statistical analysis methods are summarised in table 2. A p value <0.05 will be considered as statistically significant for all analyses and will be performed using SPSS V.25 or higher (SPSS Chicago Illinois, USA).

**Table 2 T2:** Outcomes with corresponding statistical analysis method

	Outcome	Type of data	Analysis
Primary outcome	Number of spontaneous vertigo attacks, lasting more than 20 min	Count	Generalised estimating equation

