	AAO HNS (1995) class of vertigo		Mixed model analysis
Secondary outcomes	Hearing (PTA; 0.5, 1, 2, 3 kHz and SDS)	Continuous	Logistic regression analysis
	Tinnitus (TFI)	Categorical	Mixed model analysis
	Quality of life (DHI, TFI, FLS, eQ-5D/VAS)	Categorical	Mixed model analysis
	Use of escape medication and co-interventions	Count	Logistic regression analysis
	(S)AE	Binary	Logistic regression analysis
	Cost effectiveness (iMCQ, iPCQ)	Categorical	Mixed model analysis

DHI, Dizziness Handicap Index; EQ 5DEuroQol 5DFLS, Functional Level Scale; iMCQ, iMTA Medical Consumption Questionnaire; iPCQ, iMTA Productivity Cost; PTA, pure tone average; (S)AE, (Serious) Adverse EventSDS, Speech Discrimination ScoreTFITinnitus Functional Index

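### The hearing-loss event is inconsistently specified: the decibel wording conflicts between sections, the word-score limb has no direction, and Table 2 pairs continuous audiometry with logistic regression

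*Protocol article*

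**What the plan says.** The protocol article addresses hearing in three places.

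- **Outcome measures, Hearing.** Audiometry is done at baseline, 6 and 12 months, using the four-tone average and the word recognition score. The threshold is: "A decrease of ≥10 dB or a change in word recognition score of ≥15% points is considered clinically significant". The quantity that decreases is not named.
- **Statistical analysis, text.** Logistic regression is planned for the incidence of hearing loss, together with escape interventions and adverse events. The threshold is repeated as: "A reduction in hearing of 10 decibels or a 15% change in word recognition will be regarded as a clinically significant difference". The decibel limb now points to worsening. The word-score limb still has no direction, and it is given as a percentage where the Hearing section has percentage points.
- **Statistical analysis, Table 2.** The row "Hearing (PTA; 0.5, 1, 2, 3 kHz and SDS") gives the type of data as continuous and the analysis as logistic regression.

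The same section plans mixed models for the questionnaire scores. No SD, event rate, effect or power is given for hearing. The only sample size calculation concerns vertigo control.

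**The concern.** These two sentences hold the only cut-offs from which a binary hearing outcome could be built, so whoever codes the event will use them.

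The word-score limb is the main problem. An undirected change of 15 points feeding an event called hearing loss counts a patient who gains 15 points in the same way as one who loses 15. The article gives reason to expect movement both ways. Its Introduction reports some hearing improvement, not statistically significant, in earlier intratympanic steroid trials. It also describes gentamicin as ototoxic, and gentamicin is an allowed co-intervention. If gains are commoner in one arm and losses in the other, an undirected count adds them together and can mask or distort the difference.

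The Table 2 pairing is a second problem. Logistic regression cannot be run on a continuous measurement without first cutting it, and the only cut on offer is the rule above. Measurements taken at three visits are then reduced to a yes/no, with a loss of precision.

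**Working it through.** **The plan's own figure.** The article states: "With a statistical power (1-β) of 80% and a type 1 error (α) of 5%, 67 patients per group are required". Its inputs are 87.5% and 67.5% vertigo control. With pooled variance, two-sided 5% and 80% power:

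n = [1.96·√(2·0.775·0.225) + 0.842·√(0.875·0.125 + 0.675·0.325)]² / 0.20² = 67.2 per group.

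This reproduces 67 (68 if rounded up). Multiplying 67 by 1.1 gives 73.7, hence the stated 74 per arm. The calculation says nothing about hearing. It supplies only the 67 per arm used below.

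**Word-score limb.** The SD and means are assumptions. Change is taken as normal, with a positive value meaning improvement.

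With no true change in either arm, worsening is Φ(-15/SD) and the undirected rule counts 2·Φ(-15/SD), exactly double:

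| Assumed SD (points) | Worsened by ≥15 | Counted if undirected |
|---|---|---|
| 8 | 3.0% | 6.1% |
| 10 | 6.7% | 13.4% |
| 12 | 10.6% | 21.1% |
| 15 | 15.9% | 31.7% |
| 20 | 22.7% | 45.3% |

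With a true difference (SD 12, mean change -3 on placebo and +3 on active):

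- Placebo: worsening Φ((-15+3)/12) = Φ(-1.0) = 15.9%; gain 1-Φ((15+3)/12) = 6.7%; undirected total 22.5%.
- Active: worsening Φ((-15-3)/12) = Φ(-1.5) = 6.7%; gain 1-Φ((15-3)/12) = 15.9%; undirected total 22.5%.

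A difference of 9.2 points in worsening disappears. Cancellation is exact because the means were chosen symmetric about zero. Other means would distort the difference without removing it entirely.

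**Cost of the dichotomy for the four-tone average.** Assumed: SD 15 dB, correlation with baseline 0.8, no mean change on placebo, 67 per arm, two-sided 5%.

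- Continuous, baseline-adjusted: residual SD = 15·√(1-0.8²) = 9.0 dB; SE = 9.0·√(2/67) = 1.555 dB; power = Φ(benefit/1.555 - 1.96).
- Binary (rise of ≥10 dB): SD of change = 15·√(2·(1-0.8)) = 9.49 dB; placebo rate 1-Φ(10/9.49) = 14.6%; active rate 1-Φ((10+benefit)/9.49); power by the pooled two-proportion test.

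| Benefit (dB) | Active event rate | Power, continuous | Power, binary |
|---|---|---|---|
| 4 | 7.0% | 73% | 29% |
| 5 | 5.7% | 90% | 40% |
| 6 | 4.6% | 97% | 50% |

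Simulation under the same assumptions gives 72–97% and 29–52%. A different set of assumptions leads to the same conclusion. With SD of change 10 to 15 dB, placebo worsening 0 or 3 dB and a benefit of 0.5 SD, an unadjusted continuous comparison has 82.5% power and the binary one 39–54%. To reach 80% power, the binary analysis would need 122–185 patients per arm where the continuous one needs 63.

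**The case against.** The strongest reply is that these are wording matters whose intent is clear, and much of that stands.

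- **Decibel limb.** A reader might infer that the rule itself counts improvement as deterioration. The documents do not support that. The Hearing section does not say what decreases, and the Statistical analysis section names it as hearing, beside an outcome called hearing loss. Read together they mean worsening. What remains is an inconsistency to reword.
- **Word score.** Both sentences can be read as stating only what size of change matters, with the name of the event implying its direction. That is a fair reading, so miscounting is conditional on how the rule is coded. But no sentence supplies the direction, and no other cut-off is given.
- **Table 2.** The type column may describe data as collected. Escape medication is likewise listed as a count and assigned logistic regression. This explains the label, but the only method named for audiometry still requires a dichotomy.
- **Power.** A reader might take the loss as a demonstrated defect. It is not: hearing is an unpowered secondary outcome, every input is assumed, and a directed responder event is a legitimate clinical summary.
- **Tinnitus.** It is tempting to extend the criticism to the one-point rule ("One point decrease of increase will be defined as improved or worsened tinnitus respectively"). The article gives no scoring of the Tinnitus Functional Index from which to judge a one-point step, and the scores already go into a mixed model. Only the categorical label in Table 2 is out of line.

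**Conclusion.** The point holds as an inconsistent specification of a secondary outcome that should be settled before analysis. Three things rest on the text alone: the decibel wording differs between two sections, the word-score criterion is undirected in both, and Table 2 names a method that does not fit its own data type.

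The consequences are conditional. If the undirected limb is coded into the event, it doubles the count when there is no true change under a symmetric distribution, and it can hide a real difference, as in the 15.9% against 6.7% example. The loss from dichotomising is sizeable over the assumed range, about 44 to 50 percentage points of power for a 4 to 6 dB benefit, but the documents fix none of its inputs. Nothing here affects the primary outcome or the sample size.

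**What to change.** 1. Analyse the four-tone average and the word score as continuous outcomes in the linear mixed model framework already planned for the questionnaires, with the baseline value as covariate.
2. Keep a binary hearing-loss event as a supporting analysis by logistic regression, worded identically in the Hearing and Statistical analysis sections: four-tone average risen by at least 10 dB, or word score fallen by at least 15 percentage points.
3. Report improvement (the mirror image) separately.
4. Correct Table 2 so that hearing shows the continuous measures with the mixed model and the binary event with logistic regression. Align the categorical label for the Tinnitus Functional Index with the score analysis already planned.

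The cost is wording edits in two sections and one table, plus the added mixed-model analysis of audiometry already scheduled at baseline, 6 and 12 months. No new data or patients are needed.

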#### Tinnitus

The Tinnitus Functional Index (TFI) measures the impact of tinnitus on daily life.^21^ This survey will be administered at baseline, after 6 months and after a year. One point decrease of increase will be defined as improved or worsened tinnitus respectively.^22^

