### Outcome measures

#### Vertigo

The primary outcome measure will be defined by the class of vertigo as defined by the AAO HNS 1995 guideline. The class of vertigo is defined by the average number of attacks per month during 6 and 12 months after treatment divided by the number of attacks 6 months before treatment times 100. As a result, the following class of vertigo is defined:

A: Complete control of vertigo=0.B: Substantial control of vertigo=1–40.C: Limited control of vertigo=41–80.D: Insignificant control of vertigo=81–120’.E: Worse control of vertigo >120.

Moreover, the daily attack vertigo frequency will be monitored with the aid of the DizzyQuest app (Psymate 2).^18 19^ The DizzyQuest app will be used to track the primary outcome measure, the frequency of dizziness attacks. Patients will answer daily questionnaires about their health and well-being and patients can report vertigo attacks at any time using the DizzyQuest app. Additionally, the Dizziness Handicap Inventory (DHI) questionnaire will be administered at baseline, after 6 months and after a year to assess how dizziness affects daily life.^20^ The effect of the injections in the DHI will be reported as raw data, as well as change in handicap category (mild handicap, moderate handicap or severe handicap) related to improvement, unchanged or worsened.

The following secondary outcomes will be measured.

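### The one-point TFI rule for improved or worsened tinnitus has no unchanged band or margin for measurement error, and Table 2 leaves unclear whether score or category is analysed

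*Protocol article*

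**What the plan says.** In the Protocol article, Outcome measures, Tinnitus, the instrument is introduced by what it measures: "The Tinnitus Functional Index (TFI) measures the impact of tinnitus on daily life". Timing is given as "This survey will be administered at baseline, after 6 months and after a year". The change rule is then: "One point decrease of increase will be defined as improved or worsened tinnitus respectively". A citation is attached to that rule. The section does not say whether the point is on a total, an item mean or a grade, and gives no score range.

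Two neighbouring outcomes are handled differently:
- Hearing has a margin: "A decrease of ≥10 dB or a change in word recognition score of ≥15% points is considered clinically significant".
- The DHI is reported raw and also as change of handicap category, "related to improvement, unchanged or worsened", so it has a class for no change.

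On analysis, the Statistical analysis text says "Mixed model analysis will be used to analyse differences in the questionnaire scores (DHI, TFI, FLS, eQ-5D/VAS, iMCQ, iPCQ) between the two groups". Table 2, however, carries the row "Tinnitus (TFI) Categorical Mixed model analysis". The TFI appears again in the quality-of-life row of Table 2, also typed as categorical.

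**The concern.** A self-reported score varies from visit to visit even when the condition does not. If one point of movement is enough for a label, only patients whose score moves by less than one point stay unlabelled. On any score with a wide range, that band is likely to lie inside the measurement error, and random variation is then reported as improvement or worsening.

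At stake are the improved and worsened percentages for tinnitus, a named secondary outcome. Both could be large in both arms with little clinical content, and a true difference between arms in these labels would be diluted. Because Table 2 types the TFI as categorical, and the one-point rule is the only TFI category the article defines, a reader cannot exclude that this category is what will be modelled.

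**Working it through.** The article states no misclassification rate or measurement error for the TFI, so there is no figure of its own to reproduce.

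**Inputs from the article.** A threshold of 1 point in either direction, read as a change of at least one point (Tinnitus); visits at baseline, 6 and 12 months (Tinnitus); tinnitus not obligatory for entry, since fluctuating hearing, tinnitus or fullness suffices (In- and exclusion criteria).

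**Assumed inputs.** Score range, between-patient SD, test-retest reliability r, and a normal distribution for the change in a patient with no true change.

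**Formulae.**
- Standard error of measurement: SEM = SD × √(1 − r).
- SD of the observed change D in a stable patient: s = SEM × √2.
- Share labelled changed: P(|D| ≥ 1) = 2 × [1 − Φ(1/s)], half of it in each direction.

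**Assumed 0-100 scale.** Example with SD 20 and r 0.90: SEM = 20 × √0.10 = 6.3; s = 6.3 × √2 = 8.9; share = 2 × [1 − Φ(1/8.9)] = 91%, or about 46% improved and 46% worsened. The extremes of the grid are:
- SD 15, r 0.95: SEM 3.4, s 4.7, share 83%.
- SD 25, r 0.70: SEM 13.7, s 19.4, share 96%.

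**By SEM, whatever the scale.**

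| SEM (points) | s | Labelled changed |
|---|---|---|
| 1 | 1.41 | 48% |
| 2 | 2.83 | 72% |
| 3 | 4.24 | 81% |
| 5 | 7.07 | 89% |
| 7 | 9.90 | 92% |
| 10 | 14.14 | 94% |

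The share reaches 90% at an SEM of about 5.6 points. It falls to 5% only at an SEM of about 0.36.

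**Assumed 0-10 metric.** SD 1.5, r 0.95 gives s = 0.47 and 4%; SD 2, r 0.90 gives s = 0.89 and 26%; SD 2.5, r 0.70 gives s = 1.94 and 61%.

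**Patients without tinnitus.** If a fraction f scores zero at both visits, the share is multiplied by (1 − f). For the 0-100 range of 83-96%: f = 10% gives 75-86%; f = 30% gives 58-67%.

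**Size of change that exceeds 95% of pure measurement error.** 1.96 × SEM × √2 gives 5.5 points at SEM 2, 13.9 at SEM 5 and 19.4 at SEM 7. One point is well below all three.

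**The case against.** The strongest reply is that the written analysis does not use the threshold. The Statistical analysis section applies a mixed model to questionnaire scores and names the TFI. It repeats the hearing margin but not the one-point rule, and no test of improved against worsened proportions is described. This stands: if the text governs, the harm is confined to a descriptive classification. Table 2 is weak evidence to the contrary, because its type column is loose throughout: it also types the cost questionnaires as categorical and pairs continuous hearing with logistic regression. It still contradicts the text for the TFI and needs resolving.

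Second, the unit of the point is undefined and the cited source for the rule cannot be checked here. If one point means one grade, or a point on a short scale, the rule is far less severe. This also stands, and it is why every share above is conditional. A reader might infer that almost every stable patient will be classed as changed, or that one point is the smallest step of a whole-number score. The article supports neither: it gives no range, no error and no scoring rule.

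Third, the calculation concerns patients with no true change, and their number is unknown. It therefore does not follow that the reported percentages would be mostly noise overall.

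Fourth, a wider cut need not give a more powerful comparison, since a cut near the centre of a symmetric change score can lose less information than one in the tail. That is fair. The case for a wider threshold is that the labels should mean something; the remedy for lost information is the continuous score.

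What does not fall away is that the one-point rule is stated, not left to another document, and that it has neither a margin nor an unchanged class.

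**Conclusion.** The concern holds as a flaw in a stated definition, with an unclear link to the analysis. Followed as written, the rule labels about 83-96% of patients with a measurable score and no true change, if the score runs 0-100 with SD 15-25 and reliability 0.70-0.95. The share is 48-72% at an SEM of 1-2 points and 4-61% on a 0-10 metric, and each figure falls further if some patients have no tinnitus. All of these rest on assumed scale properties and normal error.

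It would be wrong to read this as bias towards methylprednisolone or placebo. Under blinding the same error enters both arms, so both rates rise and a difference in the labels is diluted without a preferred direction. A mixed-model comparison of TFI scores is unaffected by the threshold. The primary outcome and the sample size are not touched. The issue is minor to moderate, on one secondary outcome.

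**What to change.** - State the TFI score range and that the total is analysed as a continuous score in the mixed model already described under Statistical analysis, with the baseline score accounted for.
- Correct the TFI type in Table 2 to continuous, in the tinnitus row and wherever else the TFI is listed, so that table and text agree.
- Either drop the one-point label, or replace it with a pre-specified threshold that exceeds the instrument's measurement error, giving the source of that error and an explicit unchanged class.
- Make the change before unblinding, so that the threshold is not chosen after the results are seen.

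The cost is wording only, since the scores are already collected at baseline, 6 and 12 months. The downside is a lower headline percentage of patients with improved tinnitus.

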#### Quality of life

Apart from the DHI and TFI, the EuroQol 5 dimension (EQ-5D) and EuroQol – Visual Analogue Scale (EQ-VAS) questionnaires will be used to measure quality of life at baseline, after 6 and 12 months.^23 24^ These questionnaires are standardised tests of health status that are used in economic and clinical evaluations.

#### Use of escape medication and co-interventions

In case participants remain suffering from intolerable vertigo attacks, regardless of which group they are allocated to, the use of metoclopramide and co-interventions such as intratympanic injections of gentamicin or methylprednisolone will be allowed and documented during the follow-up period. This will be based on experience of participants’ vertigo frequency and shared decision making. If patients receive additional treatment, they will not be unblinded.

